## Abstract

**Background:**

In the last decades, autologous fat grafting has been used to treat adherent dermal scars. The observed regenerative and scar-reducing properties have been mainly ascribed to the tissue-derived stromal vascular fraction (tSVF) in adipose tissue. Adipose tissue’s components augment local angiogenesis and mitosis in resident tissue cells. Moreover, it promotes collagen remodeling. We hypothesize that tSVF potentiates fat grafting-based treatment of adherent scars. Therefore, this study aims to investigate the effect of tSVF-enriched fat grafting on scar pliability over a 12-month period.

**Methods and design:**

A clinical multicenter non-randomized early phase trial will be conducted in two dedicated Dutch Burn Centers (Red Cross Hospital, Beverwijk, and Martini Hospital, Groningen). After informed consent, 46 patients (≥18 years) with adherent scars caused by burns, necrotic fasciitis, or degloving injury who have an indication for fat grafting will receive a sub-cicatricic tSVF-enriched fat graft. The primary outcome is the change in scar pliability measured by the Cutometer between pre- and 12 months post-grafting. Secondary outcomes are scar pliability (after 3 months), scar erythema, and melanin measured by the DSM II Colormeter; scar quality assessed by the patient and observer scales of the Patient and Observer Scar Assessment Scale (POSAS) 2.0; and histological analysis of scar biopsies (voluntary) and tSVF quality and composition. This study has been approved by the Dutch Central Committee for Clinical Research (CCMO), NL72094.000.20.

**Conclusion:**

This study will test the clinical efficacy of tSVF-enriched fat grafting to treat dermal scars while the underlying working mechanism will be probed into too.

**Trial registration:**

Dutch Trial Register NL 8461. Registered on 16 March 2020

## Background

The first fat grafting procedure was described in 1893 to treat a soft tissue defect for reconstructive purposes [1]. Nowadays, fat grafting is routinely used for both reconstructive as well as esthetic purposes and is far “more than volume correction alone” [2, 3]. In 2001, Zuk et al. described the adipocyte stromal cells (ASCs) that are present in large amounts in the stromal vascular fraction (SVF) of adipose tissue and possess multipotent capabilities [4]. This discovery led to an increased use of fat grafting for regenerative and scar-reducing purposes and to treat damaged tissues, such as burn wounds [5]. Since then, it is thought that observed beneficial effects are for a large part attributed to the SVF in adipose tissue.

SVF is easily obtained by dissociating lipoaspirate enzymatically or mechanically [6]. SVF comprises the non-adipocyte fraction of fat and is composed of stromal cells such as fibroblasts and other mesenchymal stromal cells as well as vasculature cells (endothelial and smooth muscle). The stromal cells produce and maintain the extracellular matrix that embeds and supports the cells in SVF. Recently, a reliable, fast, intraoperative mechanical isolation procedure has been developed to yield tissue-derived stromal vascular fraction (tSVF), which makes clinical application of tSVF more feasible than enzymatic isolated SVF (cellular SVF) [7–9]. On the one hand, tSVF probably effectuates better retention of paracrine factors through extracellular matrix components that lack in single cell suspensions like cSVF, where cells disappear through leakage of lymph vessels. On the other hand, tSVF is a unit of transplanted tissue that provides a nutritious environment, serving as a therapeutic component of adipose tissue. Case reports and retrospective studies have reported improved esthetic outcomes and pain relieve after autologous fat grafting of problematic and adherent scars [3, 5, 10–23]. These results hold promise but, besides the obvious methodological drawbacks of the study design, lack adequate scar evaluation with validated objective or subjective scar measurement tools. Moreover, physical, physiological, and psychological evaluation and measurements are also important since adherent scars cause physical burden, e.g., stiffness and impaired range of motion, and psychological burden, e.g., psychosocial distress [24, 25]. Several validated scar scales, e.g., the Patient and Observer Scar Assessment Scale (POSAS), Vancouver Scar Scale (VSS), and Manchester Scar Scale (MSS), have been developed to assess the aforementioned aspects of scar quality [26–28]. The POSAS is recognized as a highly reliable scar rating scale; moreover, it also includes the patients’ opinion and is therefore favorable for subjective scar assessment ([29], www.posas.org).

Recently, autologous fat grafting was effectively used to improve scar quality, in particular scar pliability and pain in adherent scars [30]. Scar pliability and color were assessed with validated objective measures, i.e., the Cutometer and DSM II Colormeter, and scar quality and pain with validated subjective measures, i.e., the POSAS patient and observer scales ([29, 31–37], www.posas.org). The results of the beforenamed studies warrant further research with SVF or ASCs, because these components are deemed responsible for a large part of the observed ameliorating effects on scar features [3, 5, 10–23, 30]. Moreover, enrichment of fat grafts with SVF may induce even larger and longer lasting ameliorating effects on scar features than plain autologous fat.

A well-designed clinical trial investigating these potential effects of SVF-enriched fat grafting is warranted. The aim of this study is to assess the efficacy of tSVF-enriched fat grafting in patients with adherent scars using a comprehensive scar evaluation protocol. This study will also provide benchmark data on histological change of adherent scars after tSVF-enriched fat grafting.

## Methods, design, and outcome measures

### Objectives

The aim of this study is to assess the efficacy of tSVF-enriched fat grafting in patients with adherent scars. The primary outcome measure is the change in scar pliability as assessed with the Cutometer Skin Elasticity Meter Dual MPA 580 (Courage and Khazaka GmbH, Cologne, Germany) pre- and 12 months post-tSVF-enriched grafting. The secondary outcome measures are scar erythema and melanin index, as a proxy for color and pigmentation, measured by the DSM II Colormeter (Cortex Technology, Hadsund, Denmark); scar quality assessed by the patient and observer scales of the Patient and Observer Scar Assessment Scale (POSAS 2.0); and histological features of tSVF and scar biopsies.

### Protocol and registration

This study was approved by the Dutch Central Committee for Clinical Research (CCMO) NL72094.000.20 and by the Institutional Review Boards of the participating hospitals (Red Cross Hospital, Beverwijk, and Martini Hospital, Groningen, the Netherlands). Methods of the study are specified in a protocol that is registered at the Dutch trial register (March 16, 2020, NL 8461) (https://www.trialregister.nl/trial/8461).

### Trial design

The trial design is a non-randomized early phase intra-patient, before-after trial on the effect of tSVF-enriched fat grafting on scar pliability in patients with adherent scars and who are treated in the Red Cross Hospital, Beverwijk, or the Martini Hospital, Groningen, the Netherlands (Fig. 1).

**Fig. 1 Fig1:**
[figure not shown]
Prospective cohort study design

Other study designs were considered but were not feasible for several reasons. For example, splitting a scar in two areas (one side treated with SVF-enriched fat grafting, one with plain fat grafting as the control group) may potentially lead to shifting of treatments from one side to the other, leading to unreliable results. Moreover, the effect of tSVF-enriched fat grafting or plain fat grafting may not be limited to its own area; thus, the border between both may display a gradient effect. Treating two separate scars within one patient was also considered but would exclude patients that do not have two scars and scars may possibly be not comparable. Therefore, the non-randomized study design was chosen optimum to obtain reliable results.

### Participants

Patients, aged ≥18 years with adherent scars (≥12 months old) caused by burns, necrotic fasciitis, or degloving injury, visiting the outpatient clinic of one of the Burn Centers in Beverwijk or Groningen who have an indication for fat grafting are eligible for this trial. Exclusion criteria are previous scar treatment with fat grafting, skin melanoma in patients’ history, pregnant or lactating, BMI <18 (general exclusion criteria for fat grafting procedure), unlikely to comply with the requirements of the study protocol and follow-up, and insufficient knowledge of the Dutch language (Table 1). Patients are included after they received a confirmed understandable and neutral explanation of the study by a member of the research team and after signing informed consent following the guidelines of the CCMO.

**Table 1 Tab1:** Inclusion and exclusion criteria

Inclusion criteria	Exclusion criteria
- Age ≥18 years - Patient has an adherent scar (minimum scar age: 12 months) caused by burns, necrotic fasciitis, or degloving injury, for which fat grafting is indicated - Competent adults - Patients seen by a plastic surgeon in Burn centers of the Red Cross Hospital, Beverwijk or Martini Hospital, Groningen, The Netherlands	- Previous scar treatment with fat grafting in selected scar - General exclusion criteria for fat grafting procedure: pregnancy, lactating, BMI < 18 kg/m^2^ - Skin melanoma in patient’s history - Unwillingness to commit to the study protocol and show up for all follow-up moments - Insufficient proficiency in Dutch to the extent that clear communication is not possible

### Scar selection

Before surgery, one scar area will be selected and marked according to a standardized algorithm for objective data collection (Fig. 2) [30]. The maximum size of the scar area is limited by the maximum quantity of tSVF that can be obtained and a minimum length of 2 cm will apply. Each scar consists of five measurement points. The five points in the selected area will be subjected to all study outcomes.

**Fig. 2 Fig2:**
[figure not shown]
Selected scar divided in 5 points according to a standardized algorithm

### Surgical procedure

Plastic surgeons, who have had uniform training in fat grafting procedures and are also additionally trained in Dutch burn care centers, will carry out the study procedures. The results of this study will be directly translation to real-world setting, because in clinics the procedures will be executed by a similar set of plastic surgeons with similar fat grafting skills. Under general anesthesia, lipoaspirate is harvested from the abdominal wall, flank, or thigh with fine harvesting cannulas. Out of 10 ml lipoaspirate, 1 ml of tSVF will be produced intraoperatively with the fractionation of adipose tissue (FAT) procedure, a fat dissociation procedure using a fractionator (Figs. 3 and 4) [38]. For preparing the tSVF-enriched fat graft, 10 ml lipoaspirate in a 10-ml Luer-Lock syringe will be centrifuged at 3000 rpm with a 9.5-cm radius fixed angle rotor for 2.5 min (Medilite, Thermo Fisher Scientific, Waltham, MA) at room temperature (Fig. 5). Thereafter, the upper oily layer will be drained from the top while the bottom layer will be drained by removing the lower cap of the syringe. Subsequently, in the syringe, 9.0 ml of fat graft will be left to which is added 1.0 ml of tSVF: two syringes, one with 9 ml of fat and one with 1 ml of tSVF, will be connected to a Luer-Lock and the contents will be mixed by gently pushing the content of one syringe into the other, this way yielding the tSVF-enriched fat. Small incisions at the border of the scar are created to perform adhesiolysis of the selected scar. Then, the tSVF-enriched fat (tenfold excess fat over tSVF) will be injected under the scar. This procedure is repeated until the entire scar area has reached fat grafting saturation (when enriched fat graft starts coming out of the incision holes). After fat saturation, the scar is covered and fixed with gausses. Practically, 50 ml of fat has to be harvested to yield 25 ml of fat and 2.5 ml tSVF, resulting in 27.5 ml tSVF-enriched fat graft.

**Fig. 3 Fig3:**
[figure not shown]
Flow diagram of the fractionation of adipose tissue procedure (FAT procedure)

**Fig. 4 Fig4:**
[figure not shown]
Frontal and side views of disposable fractionator with one hole of 1.4 mm inside, used to fractionate adipose tissue

**Fig. 5 Fig5:**
[figure not shown]
Lipoaspirate after performing the fractionation of adipose tissue procedure: (1) oil = disrupted adipocytes, (2) tissue stromal vascular fraction, and (3) infiltration fluid including pellet consisting of dead cell remainders

## Study outcomes

### Primary outcome measure

#### Scar pliability

The primary outcome measure is the change in scar pliability as measured by the Cutometer Skin Elasticity Meter Dual MPA 580 ® (Courage and Khazaka GmbH, Cologne, Germany) pre- and 12 months post-tSVF-enriched fat grafting (Figs. 2 and 6). The Cutometer® is a validated, reliable instrument which measures viscoelasticity of the skin by analyzing its maximal extension after inducing negative pressure ([33–37], https://www.trialregister.nl/trial/8461).

**Fig. 6 Fig6:**
[figure not shown]
The Cutometer measures scar mechanics retraction, elasticity, viscoelasticity, and maximum extension by inducing negative pressure on scar tissue (Cutometer Skin Elasticity Meter Dual MPA 580 ® Courage and Khazaka GmbH, Cologne, Germany)

### Secondary outcome measures

All scar outcome measurements will be performed by two trained observers who work independently of each other to prevent confirmation bias.

#### Scar mechanics

Scar, retraction, elasticity, viscoelasticity, and maximum extension will be measured with the Cutometer Skin Elasticity Meter Dual MPA 580 ® (Courage and Khazaka GmbH, Cologne, Germany) pre-tSVF-enriched fat grafting and 3 and 12 months post-tSVF-enriched grafting (Figs. 2 and 6) [30]. Scar pliability will also be measured after 3 months post-tSVF-enriched fat grafting.

Healthy skin measurements will be conducted as described pre-, 3, and 12 months post-tSVF grafting on the contralateral side of the treated scar. Healthy skin measurements will serve as a reference (i.e., the optimum skin mechanics within that person).

#### Scar color and pigmentation

Scar color and pigmentation will be measured with the DSM II Colormeter ® (Cortex Technology, Hadsund, Denmark), a validated and reliable tool that calculates an erythema and melanin index as a proxy for color and pigmentation (Figs. 2 and 7). Measurements of the selected scar and adjacent normal skin will be performed pre-, 3, and 12 months post-tSVF-enriched grafting [30].

**Fig. 7 Fig7:**
[figure not shown]
The DSM II Colormeter measures scar color and pigmentation by calculating an erythema and melanin index (Cortex Technology, Hadsund, Denmark)

#### Scar quality

Scar quality will be assessed by the POSAS version 2.0 ([29], www.posas.org). The POSAS Patient and Observer scales are completed pre-, 3, and 12 months post-tSVF-enriched grafting (Figs. 2 and 8). All items of the POSAS 2.0 will be scored on a 10-point rating scale and added together to obtain a final score. Additionally, item-specific scores and the overall opinion of the scar will be scored (Fig. 8).

**Fig. 8 Fig8:**
[figure not shown]
The POSAS Scale 2.0. The patient score combines scar pain, itch, color, stiffness, thickness, and irregularity. The observer scale comprises of the items vascularity, pigmentation, thickness, relief, pliability, and surface area. All items of the patient and observer score combined will form a total POSAS score (the highest score represents the worst scar imaginable). It also consists of an overall opinion of the scar

#### Standardized photographs

A standardized photograph will be taken from each scar within 24 h before treatment under the same light and camera conditions each time.

#### Histological analyses

For participants in our study, scar biopsies are optional. If patients consent to biopsies, histological features will be assessed by taking a 2-mm biopsy of the selected scar on a fixed position: 1 cm left from point 1 within 24 h before treatment and at 12 months post-tSVF-enriched grafting 1 cm right from point 1 (Fig. 2). The skin sample will be fixed with 2% PFA and paraffin embedded. From each patient, 0.5 ml of tSVF will be 2% paraformaldehyde (PFA) fixed. Fixed samples will be transported to the University and Medical Center Groningen for histological analysis. There, thin sections of paraffin-embedded scar biopsies and tSVF will be deparaffinized and stained with H&E, Picrosirius red (extracellular matrix collagen), CD68 (macrophage infiltration), perilipin A antibodies (presence of residual adipocytes), alpha-smooth muscle actin antibodies (smooth muscle cells and myofibroblasts), and von Willebrand Factor and/or CD31 (endothelial cells). Stained sections will be scanned and subjected to image densitometry for quantification.

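### The fixed biopsy positions span 2.2 cm but the selected scar area may be only 2 cm long, and the fixed left-then-right order leaves position inseparable from time

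*Protocol article*

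**What the plan says.** Under Scar selection, the Protocol article has one area marked before surgery and sets a lower size limit: "a minimum length of 2 cm will apply". There is no upper limit in centimetres: "The maximum size of the scar area is limited by the maximum quantity of tSVF that can be obtained". The same section states: "Each scar consists of five measurement points". Their layout is in Fig. 2, which is not shown in the text available.

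Under Histological analyses, biopsies are voluntary: "For participants in our study, scar biopsies are optional". For patients who consent, histology rests on "taking a 2-mm biopsy of the selected scar on a fixed position". The baseline and follow-up samples are placed as follows: "1 cm left from point 1 within 24 h before treatment and at 12 months post-tSVF-enriched grafting 1 cm right from point 1". The section gives no rule for scars too small for these offsets and does not vary the side between patients.

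Histology of tSVF and of scar biopsies is listed among the secondary outcomes under Objectives. The Discussion relies on it for insight into the mechanism.

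**The concern.** Two stated rules do not fit together. One fixes both biopsy positions at an absolute distance from a reference point; the other admits areas shorter than the span those positions need. This is not a detail left to another document, because the article calls the position fixed.

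The second issue is the order. Every baseline sample comes from the left and every 12-month sample from the right. The trial is a single-group before-after study, so no control arm could reveal a positional artefact. If left and right differed systematically, the paired comparison would report that difference as change over time, and no later analysis could remove it.

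At stake is the reading of the histological change, which the article offers as benchmark data and as a window on the mechanism. A 2-mm sample quantified by image densitometry could be sensitive to partial inclusion of tissue other than treated scar.

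**Working it through.** **Inputs.** Minimum length of the selected area: 2 cm (Scar selection). Offsets: 1 cm to each side of point 1, and biopsy size 2 mm (Histological analyses). Assumption: 2 mm is the punch diameter, so the radius is 0.1 cm.

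**The plan's own figure.** No sample size or power is given for histology. The stated size for the primary outcome reproduces. A two-sided paired t-test at 0.05 with standardised effect 0.45 needs n = 41 (power 0.803), and 41 / 0.9 = 45.6, hence 46. Nothing below changes this.

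**Span of the two punches.**
- Centre to centre: 1 cm + 1 cm = 2.0 cm.
- Outer edge to outer edge: 2.0 cm + 2 × 0.1 cm = 2.2 cm.
- Shortfall at the minimum: 2.2 − 2.0 = 0.2 cm.

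**Dependence on point 1.** Let L be the left-right extent of the area through point 1, and a the distance from point 1 to the left border. The left punch is wholly inside if a ≥ 1.1 cm, and the right punch if L − a ≥ 1.1 cm. Both hold only if L ≥ 2.2 cm. With L = 2.0 cm:
- Point 1 central (a = 1.0): each punch is centred on the border, and about half of each lies outside (straight border assumed).
- Point 1 displaced 0.1 cm to the right (a = 1.1): the left punch is wholly inside. The right border is 0.9 cm from point 1 and the right punch covers 0.9 to 1.1 cm, so it is wholly outside.
- Point 1 displaced 0.1 cm to the left: the reverse.

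So with L = 2.0 cm no position of point 1 accommodates both. With L = 2.2 cm both just fit if point 1 is central; at 3 cm there is 0.8 cm of slack.

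**Side and time.** Take a model with one term per patient, one for time and one for side. With 20 illustrative patients it has 20 + 1 + 1 = 22 columns. As written, side equals time in every patient and the rank is 21, so the two effects cannot both be estimated. If the first side is alternated between patients, the rank is 22.

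**What the aliasing could do.** Suppose there is no true change, and a systematic left-right difference expressed in SDs of the paired differences. The rejection rate of a two-sided paired t-test at 0.05, used here as an illustration, is:

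| Assumed left-right difference (SD) | n = 20 | n = 41 |
|---|---|---|
| 0 | 0.05 | 0.05 |
| 0.1 | 0.07 | 0.10 |
| 0.2 | 0.14 | 0.24 |
| 0.3 | 0.25 | 0.47 |
| 0.5 | 0.57 | 0.88 |

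The SD values and n = 20 are assumptions; n = 41 would require biopsies in as many patients as the primary analysis needs. The documents give neither a side difference nor a number of biopsies, and the first row is as compatible with them as any other.

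**The case against.** A reader might infer that the histological change is contaminated. The documents do not support that. Aliasing biases the mean change only if left and right differ systematically across patients. Nothing in the article suggests they do, and the scars have several causes. Without such a difference, sampling 2 cm apart adds within-scar variability and costs precision, but leaves the mean unbiased and the error rate at 0.05. Randomising the side would not remove that variability. Using a second position also has a merit: it avoids re-sampling the healed site of the first biopsy.

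A reader might also infer that a 12-month sample at the margin would imitate collagen normalisation. That needs the right-hand punch to lie further out than the left. With point 1 central, both are affected alike and the change is diluted; with point 1 displaced to the left, the shift runs the other way. The visible text favours none of these.

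The misfit itself carries a proviso. Fig. 2 is not shown, so how left and right relate to length is unknown. If the 2 cm is measured across the left-right line, an area wider than it is long could hold both punches. The selected area may also be part of a larger scar, so a punch beyond its border may still be in scar, though possibly untreated scar.

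Reach is limited too. Biopsies are optional, histology is one of several secondary outcomes, and the practical graft volume of 27.5 ml under Surgical procedure suggests that many scars are larger than the minimum, though that is only an inference. The lack of a control group limits the mechanism claim far more, and randomising the side would not isolate a tSVF effect.

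These points narrow the consequence. They do not remove the conflict between the two stated rules, or the fact that the side order is fixed for every biopsied patient.

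**Conclusion.** The concern holds as a minor point in two parts.

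First, the biopsy rule cannot be met in the smallest eligible areas: it needs 2.2 cm where 2 cm is allowed. This assumes that 2 mm is the diameter and that length means the longest or the left-right dimension. The effect on the histological change is dilution if both punches are affected equally, or a shift in either direction if point 1 is off-centre. The share of scars involved cannot be derived from the documents.

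Second, side and time are completely aliased in every biopsied patient. This is an avoidable risk whose size depends on a left-right difference for which there is no evidence; if that difference is zero, there is no bias.

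Both parts concern only the optional scar histology. The primary outcome and the planned 41 evaluable and 46 included patients are unaffected.

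**What to change.** Reconcile Scar selection with Histological analyses in one sentence. Either define the offset so that both punches fall wholly inside the selected, treated area, for example by scaling it to the area's extent, or keep the 1 cm offset and analyse histology only in scars wide enough for it (at least 2.2 cm along the left-right line with point 1 central, more if it is off-centre). State which dimension the 2 cm minimum refers to.

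Randomise per patient which side is biopsied first, with the opposite side at 12 months. This keeps the two separate sites and makes a side effect estimable.

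The cost is the added sentence and a pre-generated left/right list. No extra biopsies or patients are needed. Restricting the analysis to wider scars would make the optional subset slightly smaller.
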